### **9.7 Subject population**

The subject population includes all adult patients on in-centre, maintenance HD or HDF for ESKD. Our exclusion criteria are:

- Lacks capacity to consent;
- Clinician predicted prognosis of less than 3 months;
- Started maintenance HD or HDF within 4 weeks;
- Transition to living kidney donor transplant or home dialysis scheduled within 3 months;
- Not suitable for high-volume HDF for other clinical reasons such as dialysis less than thrice weekly or unlikely to achieve sufficient blood flow rates with current vascular access, or prior intolerance of HDF.

All randomised participants will be included in intention-to-treat analyses.

A per protocol analysis will also be conducted of the primary outcome where patients are censored at the time of cross-over and adjustment will be made for baseline characteristics.

### **9.8 Procedure(s) to account for missing or spurious data**

Where missing data exist the frequency of missing data will be indicated and if the amount of missing data differs substantially between treatment groups (>10%) potential reasons will be explored. Sensitivity analyses will be conducted (including the use of multiple imputation methods where assumptions are met) to examine the influence of missing data on the key trial findings.

### **9.9 Other statistical considerations**

A detailed statistical analysis plan will be developed for the approval of the TSC prior to analysis. Any deviation(s) from the approved plan will be described and justified to the TSC for their approval.

### **9.10 Economic evaluation**

There is limited evidence on the cost-effectiveness of high-volume HDF compared to high-flux HD. Previous work alongside the CONTRAST trial which compared online HDF with low-flux HD has not

provided conclusive evidence (24). Cost-utility data were only collected on 409 of 714 patients randomised in CONTRAST. The CONTRAST trial suggested that HDF was marginally more costly than low-flux HD over a 3-month period (€88,622 vs €86,086), primarily due to the higher cost of disposable equipment and water purity control. Over 5 years of follow up quality adjusted life years (QALYs) were also marginally higher (2.40 vs 2.34) in patient receiving HDF. The incremental cost per quality-adjusted life year (QALY) of HDF versus HD was €287,679, indicating that it would not be cost-effective. A subsequent post-hoc subgroup analysis (n=130) from a Canadian CONTRAST site that achieved high-volume HDF in the majority of its participants reported significantly higher QoL in patients on high-volume HDF. They concluded that the additional costs of high volume HDF were largely due to increased survival and that these costs were justified by better outcomes (\$CAN 32,112 per QALY gained) (25). Due to the high costs of RRT, it is very important to provide more definitive evidence on the cost-effectiveness of high volume HDF to determine whether it should be more widely adopted on the NHS.

The primary economic analysis will take an NHS perspective in order to minimise the participant burden and increase efficiency of the RCT. Additional analyses will explore any impact of treatment on residential care. . This will be based on brief resource use questions collected directly from patients. The analysis will include a 'within trial' analysis estimating cost-effectiveness during the trial follow up period. The costs associated with high-flux HD and high-volume HDF will be determined by calculating the incremental cost of equipment, staff-time, and materials/consumables used in performing dialysis. Healthcare resource use, including hospital visits and admissions, GP and community care contacts, and medication use will be obtained from linked hospital statistics in England, Scotland, and Wales, as necessary, the UK Renal Registry, and patient self-completed questionnaires and evaluated using published unit cost sources .Should differences in any component of the primary outcome between the study groups be evident at the end of trial follow-up , resulting in uncertainty over the longer-term cost-effectiveness estimates of HDF, we will develop a probabilistic decision analysis model to extrapolate cost-effectiveness estimates over patient lifetimes. Further details of the economic analysis will be provided in a publicly available health economic analysis plan.

Source data for the economic evaluation include UKRR, hospital statistics (HES, PEDW, ISD), and patient reported quality of life and healthcare and medication use as described in previous sections of the protocol.

We will annuitize the capital costs (e.g. machine) of HDF and HD based on purchase price, useful life, discount rates, resale value and estimate the cost per dialysis visit based on dialysis time and annual throughput (46). We anticipate that patients receiving HDF will have more

advanced dialysis machines capable of monitoring blood flow and concentration, although this will not be the case at all sites. We will obtain typical unit costs for consumables (e.g. blood lines, ultra-pure water, reinfusion line, microbiological testing, etc.) from a survey of participating dialysis units. We will use observations at purposively selected sites to collect data on resources (e.g. machine set up time) not routinely recorded. Using these data we will micro-cost dialysis sessions using methods similar to those previously published by our research team (47). Medication costs (e.g. Erythropoiesis stimulating agents and phosphate binders) will be estimated from the British National Formulary. National unit costs will be used to value hospitalisations, GP and community care (48, 49).

As HDF and HD require dialysis with similar frequency and duration, we do not expect any major impact on patient/family expenses. However, there is a small possibility that patients may need more residential care in one arm over the other. Therefore, our analysis focusses on the NHS perspective and we will include a secondary analysis looking at NHS and residential care. QALYs will be estimated from EQ-5D-5L responses and mortality data during follow up, accounting for any baseline differences in EQ-5D-5L scores. Missing cost and QALY data may be imputed using simple or multiple imputation methods. Cost and QALY data will be combined to calculate an incremental cost-effectiveness ratio (ICER) and incremental net monetary benefit (INMB) statistic (50). For each individual  $i$ , the NMB is the willingness to pay for a QALY,  $\lambda$ , multiplied by the patient outcome  $E_i$  (i.e. QALYs), minus the cost of health care  $C_i$ ;  $NMB_i = \lambda E_i - C_i$ . In the primary analysis we will estimate whether HDF is cost-effective at the established NICE threshold of £20,000 per QALY gained. Uncertainty in the point estimate of cost per QALY will be quantified to calculate confidence intervals around the ICER and INMB. The probability that HDF is cost-effective at various 'willingness to pay for a QALY' thresholds and in the pre-specified subgroups (residual renal function and age) will be depicted using a cost-effectiveness acceptability curve (51).

If appropriate, a probabilistic decision analysis model will be developed and populated with many parameters estimated directly in the RCT (e.g. short-term hazard rates and ratios for mortality, peritoneal dialysis, transplant, hospitalisation; costs and utility scores for HDF and HD). Other parameters (e.g. long-term hazard rate of mortality, peritoneal dialysis, transplant, hospitalisation after HD) will be estimated based on registry data and a rapid review of the epidemiological literature of longitudinal studies and implemented using a Markov model. The model will predict the time-variant probability of patient transition through a small number of health states (e.g. HD/ HDF, PD, transplant, death) and the costs and quality of life associated with those health states. Access to HES-CR linked individual patient registry data will be a

significant advantage in this regard, allowing us to fit the most appropriate models for long-term survival and disease progression.

## **10 DATA HANDLING**

### **10.1 Data collection tools and source document identification**

Baseline data will be entered directly into a case report forms (CRF) and sent securely (by post or electronically) no more than 4 weeks after the baseline visit to the CTU for entry into the database. Baseline patient questionnaires (PQs) will be administered by the research staff at the baseline visit and returned to the CTU for entry into the database; thereafter, PQs will be sent out 6-monthly by the CTU to the patient with an enclosed cover letter signed by the site principal investigator and research nurse and returned directly to the CTU. If a patient questionnaire is not returned, up to 2 reminders will be sent. Where appropriate questionnaires can be administered by telephone from the CTU to get responses from the patient to the EQ5D questions.

Standardised tools are being used:

- Co-morbidity: Davies co-morbidity Score (52) & Charlson co-morbidity index (53)
- Quality of life: EQ-5D-5L (54), and DSI (55).

A central administrative database will be set up by BTC that prompts the CTU when PQ forms are due.

PIs must keep records of all participating patients (sufficient to link records e.g., CRFs and hospital records), all original signed informed consent forms and copies of the CRF pages.

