| Post approval | 8.0 | 3 May 2022 | [name] | 
1) The Bristol Randomised Trials Collaboration (BRTC) Clinical Trials unit is Bristol Trials Centre (BTC) with effect from 16/12/2021. All references to BRTC have been replaced with BTC.
 
2) Name change of National Institute for Health Research to National Institute for Health and Care Research in April 2022 (page 9)
 
3) Addition of 'Blood stream infections' to Table 2. (36-37)
 
4) Addition of details relating to adherence to protocol, plans to promote participant retention and complete follow-up, data management and data flow within the study (page 38-39)
 
5) Adverse events screening timelines and making clear that these are directed by the DMC (page 47).
 
6) Update of the Statistical analysis plan to take into account sensitivity analysis, subgroup analysis and interim analysis as agreed by TMG for the protocol paper publication (page 52-53)
 
7) Procedure to account for missing data updated to account for amount of
 |

|  |  |  |  |                                                                                                                                                                                                                                                                                                                                 |
|--|--|--|--|---------------------------------------------------------------------------------------------------------------------------------------------------------------------------------------------------------------------------------------------------------------------------------------------------------------------------------|
|  |  |  |  | 
missing data (>10%) with potential reasons will be explored (page 55).
 
8) The option to administer questionnaires by telephone by the CTU to get responses from the patient to the EQ5D questions (page 59).
 
9) Appendix 1 table updated to make contents clearer e.g. added column headings (page 71).
 |
|--|--|--|--|---------------------------------------------------------------------------------------------------------------------------------------------------------------------------------------------------------------------------------------------------------------------------------------------------------------------------------|

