#### 3.5 Secondary endpoints/outcomes

- All-cause mortality (UKRR & CR)

- Non-cancer mortality (CR)
- Cardiovascular - cause-specific hospitalisation & mortality (UKRR, Hospital Statistics (HES, PEDW, ISD & CR)
- Infection - cause-specific hospitalisation & mortality (UKRR, Hospital Statistics & CR) and reportable infections (MRSA & MSSA) (Public Health England)
- Health related quality of life – preference-based quality of life derived from EQ-5D-5L,, disease specific quality of life (Dialysis Symptom Index) and time to recover after each dialysis  (5)
- Indirect effects: routinely measured/ prescribed and recorded anaemia disorder management (haemoglobin levels and erythropoiesis stimulating agent dose), mineral bone disorder management (calcium, phosphate and PTH levels and phosphate binder dose) and nutritional status (albumin level) (UKRR)
- Cost-effectiveness from an NHS perspective and a second NHS & residential care perspective i.e. nursing home, residential home and hospice care whether for respite or permanent residence (UKRR, Hospital Statistics for in-patient and out-patient activity & targeted resource use questions for primary care, residential care, and medication usage )
- Impact on the environment, including locally purified water, manufactured saline and plastic consumables
- Water quality testing and breaches

---

 Answer to question “How long does it take you to recover from a dialysis session?”

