|----------------------------------|-----------------------------------------------------------------------------------------------------------------------------------------------------------------------------------------------------------------------------------------------------------------------------------------------------------------------------------------------------------------------------------|------------------------------------------------------------------|
|                                  | Shock (249), Skin and subcutaneous tissue infection (197), Fever of unknown origin (246), Infective arthritis and osteomyelitis (201), Bacterial infection; unspecified site (3), Other inflammatory condition of skin (198), Other infections; including parasitic (8), Influenza (123), Urinary tract infections (159), Genitourinary symptoms and ill-defined conditions (163) |                                                                  |
| Mortality data                   | Non-cancer mortality (i.e. all causes of death excluding chapter II causes in ICD-10).                                                                                                                                                                                                                                                                                            | NHS Spine tracing, UKRR, Hospital Statistics, Civil Registration |
| Patient reported outcomes        | EQ-5D-5L, DSI and Time to recovery (following dialysis) (5).                                                                                                                                                                                                                                                                                                                      | Patient questionnaire administered 6 monthly                     |
| RRT use                          | Frequency, machine, dialyzer, dialysis times and consumables used.                                                                                                                                                                                                                                                                                                                | Annual census (extracted from the renal IT system).       |

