| Other hospital admissions | Day case and inpatient hospital admissions (including surgical procedures performed),                                                                                                                                                                                                                                                                                             | Hospital Statistics (HES, PEDW, ISD)                             |
| Patient reported healthcare use  | Nursing home/residential home days/hospice days, and primary care, community services and medication usage in the last 6 months.                                                                                                                                                                                                                                                  | Patient questionnaire administered 6 monthly                     |
| Blood stream infections          | Methicillin resistant staphylococcus aureus, Methicillin sensitive staphylococcus aureus, Clostridium difficile, and Escherichia coli, as report by mandate to PHE/ the UKHSA                                                                                                                                                                                                     | Reported to PHE/ UKHSA and shared with UKRR                      |

Numbers in parentheses following diagnoses refer to the Healthcare Cost and Utilisation Project Clinical Classification System for mapping diagnoses onto ICD-10 [www.hcup-us.ahrq.gov](http://www.hcup-us.ahrq.gov).  
Abbreviations: HES = Hospital Episode Statistics; ICD = International Classification of Diseases; ISD =

Information Services Division; PEDW = Patient Episode Database for Wales; PHE=Public Health England; UKHSA = UK Health Security Agency; UKRR = UK Renal Registry

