#### **Plans to promote participant retention and complete follow-up**

As the primary outcome relies on data linkage with national routine healthcare databases, participants will only be lost to follow up if they opt out of data linkage after being randomised. Patients who discontinue allocated treatment can choose to continue to receive questionnaires and allow data linkage. The minimum number of identifiers will be used to link with routine data sources, as agreed with those organisations and set out in the participant information sheet. For patient-reported outcomes, up to three reminders are sent.

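### The protocol gives two different reminder limits for the same 6-monthly questionnaire, and its telephone option is written for EQ-5D alone, so a round completed only by telephone yields no recovery-time answer and no residential-care use.

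*Protocol*

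**What the plan says.** **Reminders.** Under the heading on participant retention and complete follow-up, within section 7.6: "For patient-reported outcomes, up to three reminders are sent". In section 10.1, on the questionnaires sent out every six months by the trials unit: "If a patient questionnaire is not returned, up to 2 reminders will be sent".

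**Telephone.** The next sentence of section 10.1 reads: "Where appropriate questionnaires can be administered by telephone from the CTU to get responses from the patient to the EQ5D questions". The version 8.0 entry in the version table (3 May 2022) describes the same scope: "The option to administer questionnaires by telephone by the CTU to get responses from the patient to the EQ5D questions". Section 7.6 offers paper and web-portal completion and does not mention the telephone.

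**What the questionnaire carries.** Section 3.5 names, besides EQ-5D-5L, "disease specific quality of life (Dialysis Symptom Index) and time to recover after each dialysis" as secondary outcomes. A footnote shows that recovery time is the answer to one question. Table 2 gives the 6-monthly patient questionnaire as the source for all three patient-reported measures. It gives the same source for "Nursing home/residential home days/hospice days, and primary care, community services and medication usage in the last 6 months". Appendix 1 shows no follow-up visits and ticks these patient-reported outcomes and residential-care days under the questionnaire column, not under linkage.

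**Provision for missing data.** Section 9.8 requires the frequency of missing data to be shown and reasons to be explored if it differs by more than 10% between groups. It also plans sensitivity analyses, with multiple imputation where its assumptions are met.

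**The concern.** The two sections set different amounts of chasing for one instrument. The trials unit needs a single rule. Participants and treating staff are unblinded, so effort to obtain patient-reported data should be fixed and the same in both arms.

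The telephone text is a separate matter. A call is made and the patient is on the line, but the stated purpose is to obtain EQ-5D answers. Recovery time is a named secondary outcome that takes one question, and no other route is listed for it in follow-up. Residential-care use supports the second economic perspective (NHS plus residential care) in sections 3.5 and 9.10 and also has no other listed follow-up source. For a round completed only by telephone, the EQ-5D analysis has a value while the recovery-time analysis does not. In the economic analysis, the utility is known but residential-care cost is not, although net monetary benefit needs both for the same person.

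The protocol treats questionnaire response as a practical problem: version 7.0 shortened the questionnaire to improve it, and version 8.0 added the telephone option.

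**Working it through.** The protocol states no figure on this point to reproduce. The check is a comparison of texts with a little counting.

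**1. Reminder limits (inputs: sections 7.6 and 10.1).**
- Under section 7.6: 1 initial mailing + 3 reminders = at most 4 contacts per round.
- Under section 10.1: 1 initial mailing + 2 reminders = at most 3 contacts per round.
- Difference: 4 − 3 = 1 contact per round for a patient who does not reply.

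Both are ceilings, but they are different ceilings for the same mailing.

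**2. What a telephone-only round delivers (inputs: section 10.1, Table 2, Appendix 1).**

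| Item | Listed follow-up source | Within the stated purpose of the call? |
|---|---|---|
| EQ-5D-5L | 6-monthly questionnaire | Yes |
| Time to recovery (one question) | 6-monthly questionnaire | No |
| DSI | 6-monthly questionnaire | No |
| Residential-care days | 6-monthly questionnaire | No |
| Primary outcome events | Linked routine data | Not applicable |

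If a proportion *p* of expected rounds is completed only by telephone, completeness of recovery time and residential care is lower than that of EQ-5D by exactly *p*. The protocol does not give *p*, so no size can be attached.

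**3. Rounds exposed (inputs: version 8.0 dated 3 May 2022; recruitment 01/11/2017 to 30/09/2022; follow-up to 31/05/2025; 6-monthly questionnaires).**
- Window from version 8.0 to the end of follow-up: 3 May 2022 to 31 May 2025, about 37 months. 37/6 = 6.2, so a participant already in the trial has 6 or 7 due dates in the window.
- Last recruits (30/09/2022): 32 months of follow-up. 32/6 = 5.3, so 5 rounds (months 6 to 30).
- First recruits (01/11/2017): 91/6 = 15.2, so 15 rounds in all. They had passed month 54 by 3 May 2022 (54/6 = 9 rounds already due), leaving 15 − 9 = 6.

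The exposed range is therefore about 5 to 7 rounds per participant who survives to the end of follow-up. This counts from the date version 8.0 was issued; later implementation at the trials unit would shorten it.

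**The case against.** The strongest reply is that the telephone option takes nothing away. Without it, a non-responder contributes no EQ-5D, no DSI and no recovery time; with it, EQ-5D is rescued and the rest is no worse. EQ-5D feeds the QALYs, so giving it priority is understandable. A short call is in keeping with the decision to shorten the questionnaire. Longer calls may be completed less often, and asking a symptom inventory by interview in an open-label trial introduces a mode effect. This is sound as far as the DSI goes, and it is why telephone DSI is left optional below. It is weak for recovery time and residential care, which add little to a call already being made.

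It can also be said that section 10.1 states a purpose and does not forbid other questions, and that it does not call the telephone a last resort after reminders. Both are true. Reading it as a fallback is natural, because the sentence follows directly on the reminder rule, but it remains a reading. The text still names only EQ-5D, and no other section widens it.

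On reminders, the reply is that one mailing per round is a small difference and that no outcome definition or analysis depends on it. That is accurate, but the contradiction remains.

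A reader might go further and infer that recovery-time and DSI results will be biased between arms, or will describe only fitter patients. The protocol does not support this. Nothing in it shows that patients reached by telephone are frailer or that their share differs by arm. Section 9.8 plans for missing data, section 9.3.3 plans repeated-measures models adjusted for the baseline value, and telephone EQ-5D answers could help to impute the missing measures. A reader might also take the gap to run over all 5 to 15 rounds of follow-up; the date of version 8.0 rules that out.

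**Conclusion.** Both parts hold in limited form. The reminder limits in sections 7.6 and 10.1 contradict each other, by one contact per round, and must be reconciled. The telephone text, read as written, leaves a one-question secondary outcome and the residential-care input uncollected in any round completed only by telephone.

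The consequence is an avoidable loss of completeness in secondary patient-reported and economic outcomes over about 5 to 7 rounds per participant. Its size is unknown, because it equals the unreported telephone share. The analyses in section 9.8 reduce the consequence, but imputing a single-item answer is a poor substitute for asking for it. The conclusion assumes that calls follow the stated EQ-5D purpose and that a patient completed by telephone does not also return the questionnaire for that round.

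**What to change.** - **Reminders:** state one maximum number, identical in sections 7.6 and 10.1, and say that it applies to both arms. The trial team should choose the number; the protocol gives no ground for preferring either.
- **Telephone:** in section 10.1, state that the call collects EQ-5D-5L, the single recovery-time question and the residential-care item, with the DSI optional. Add the telephone to the completion modes listed in section 7.6.
- **Mode:** record for each round whether completion was on paper, online or by telephone, so that the share can be reported by arm and mode examined in sensitivity analyses.

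The cost is a wording change in two sections, one extra field in the database and slightly longer calls. If the higher reminder limit is chosen, there is also at most one more mailing per unreturned questionnaire than section 10.1 now allows. The downside is mixed mode of completion for recovery time and residential care, which EQ-5D already has under the present text.
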